### Additional secondary endpoints for children aged 4 years and older:

Only applicable for patients able to perform technically acceptable (and reproducible) pulmonary function tests.

- The forced expiratory volume in one second (FEV1) and the forced vital capacity (FVC) measured 30 minutes post IMP will be compared to pre-dosing FEV1 and FVC values at visit 2.
- Trough FEV1 and through FVC response will be determined at visit 3, visit 4, visit 5 and visit 7. Trough FEV1 is defined as the FEV1 and FVC measured approximately 24 hours after the last IMP inhalation. Response is defined as a 10% improvement in FEV1 or FVC, respectively, compared to baseline (visit 2, pre-dosing).
- Potential biomarkers for treatment response (Eosinophils, IgE, specific IgE to common allergens: birch, grass, *Dermatophagoides pteronyssinus*, *Alternaria*, *Cladosporium*, cat,

dog, hen's egg, cow's milk and peanut)

**Assessment of safety:** Safety will be ensured by analysis of symptom scores and rescue medication by electronic diary, and AEs.

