| SECONDARY ENDPOINTS  | 
Key secondary endpoint(s): number of severe exacerbations, number of hospitalizations (severe exacerbation), (severe) exacerbation-free survival time, number of asthma-related events defined by use of antibiotics, percentage of night-time awakenings due to asthma symptoms as assessed by the electronic patients diary/PACD, percentage of days without asthma symptoms assessed by TIPP diary App (PACD), , percentage of days and episodes of > 3 days with use of PRN salbutamol rescue medication, health utilization (number of physician visits), number of missed days in daycare, result of TRACK, CGI-C at end of treatment and potential biomarkers for treatment response:
 
Eosinophils, IgE, specific IgE to common allergens (birch, grass, Dermatophagoides pteronyssinus, Alternaria, Cladosporium, cat, dog, hen's egg, cow's milk and peanut.
 
Assessment of safety:
Safety will be ensured by analysis of symptom scores and rescue medication use by the electronic diary, and adverse events (AEs).
                                                                                                                                                  |
| STATISTICAL ANALYSIS | 
Efficacy:
The comparison between groups will be made by time to first severe exacerbation within 12 months of therapy.
 
Description of the primary efficacy analysis and population:
The time to first severe exacerbation will be analyzed by Cox regression with factor treatment and the covariates age group and center. Analyses will be performed in the intention-to-treat population and repeated in the per-protocol population as sensitivity analyses. Treatment differences will be displayed by hazard ratios and 95% confidence intervals.
 
Safety: For safety analyses, frequencies of patients experiencing at least one adverse event (AE) will be displayed by system organ class and preferred term according to MedDRA terminology.
 
Secondary endpoints:
For secondary analyses, Cox regression for time to event data will be used and negative binomial regression for count of events. Further secondary endpoints will be assessed by chi-square or Fisher's exact test for categorical variables or t-test or Mann-Whitney-U-test for continuous variables.
 
All tests will be conducted on a two-sided significance level of alpha = 0.05.
 |

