| Assessment of asthma control (GINA)                         |        | x                             | x                         |            | x           |                      | x           |                      |             |                      | x                      |
| Adverse events (AE)                                                     |        | x                             | x                         | x          | x           | x                    | x           | x                    | x           | x                    | x                      |
| Concomitant therapy                                                     |        | x                             | x                         | x          | x           | x                    | x           | x                    | x           | x                    | x                      |
| Trial completion                                                        |        |                               |                           |            |             |                      |             |                      |             |                      | x                      |

1. Hematology and blood chemistry. Topical (percutaneous) analgesia to reduce pain associated with venipuncture, e.g. amethocaine gel or EMLA cream (Eutectic Mixture of Local Anesthetics), must be applied (may only be omitted in patients who explicitly refuse it). A maximum of 3 puncture attempts to obtain blood (approx. 5 mL) will be performed. Visit 1 laboratory parameters comprise: differential blood count, glutamate-pyruvate-transaminase (GPT), glutamate-oxalate-transaminase (GOT), alkaline phosphatase (AP), urea, creatinine levels and total serum IgE and specific IgE to birch, grass, *Dermatophagoides pteronyssinus*, *Alternaria*, *Cladosporium*, cat, dog, hen's egg, cow's milk and peanut. All parameters will be documented in the electronic Case Report Form (eCRF). PaxGene tubes for miRNA will only be sampled at V1.
2. Spirometry/ Oscillometry will only be performed in children  $\geq 4$  years who are capable of providing spirometry / oscillometry of acceptable quality. To confirm acceptable quality, spirometry / oscillometry measurements will be performed in patients  $\geq 4$  years if they are capable of providing measurements of acceptable quality (with a mouthpiece) and if the required equipment is available at site.

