### **Pulmonary Function Testing**

#### **a) Spirometry**

PFTs will only be performed in  $\geq 4$ -year-olds who are capable of providing PFTs of acceptable quality. Repeatability criteria for preschoolers should be used: The patient should produce at least two acceptable curves, where the second-highest FVC and FEV1 are within 0.1 L or 10% of the highest value, whichever is greater (56). In a recent own investigation we found the following: According to the new American Thoracic Society/European Respiratory Society (ATS/ERS) guidelines, 74.6% of the children aged 4–6 years could perform at least 2, repeatable measurements in the healthy status (57, 58).

PFTs will be recorded whilst the patient is in a sitting position at the time points specified in the study flow chart. Spirometry will be performed according to the ERS. All lung function tests will

be repeated until three technically acceptable measurements have been made and the best of these three measures will be recorded in the CRF. The following variables will be documented: VC [L, % pred], FEV1 [L, % pred], FVC [L, % pred], FEV1/FVC (Tiffenau-Index).

Calibration of spirometry equipment is mandatory on all visit days and calibration logs should be stored as source data. The spirometers and their use, including daily calibration, must meet ATS/ERS criteria (57). If necessary, the sponsor may provide a SOP to the centers.

b) Impulse oscillometry

Impulse oscillometry (IOS) is a breathing analysis at rest that requires little cooperation. Thus, it can be performed in relatively young children. IOS parameters can differentiate between central and peripheral airways. There is evidence that asthma exacerbations in infancy are related to an inflammation of the small airways. In an own study, we included 75 children aged 4–7 years with mild asthma in the infection-free interval in the summer (58). The results showed that the IOS predicted significantly mild asthma exacerbations in autumn and winter (AUC: Rrs5 78%, Xrs5 70%, and Rrs5-20 77%). This was not the case for spirometry (FEV1) and methacholine provocation (both AUC 61%).

c) IOS measurement

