### 8.3.2 Analysis of secondary endpoints

The number of severe exacerbations, the number of hospitalizations as well as the number of asthma-related events defined by use of antibiotics will be assessed by negative binomial regression with time within study as offset variable. Exacerbation-free survival time will be analyzed by Cox regression. Further secondary endpoints will be assessed by chi-square or Fisher's exact test for categorical variables or t-test or Mann-Whitney-U-test for continuous variables.

All tests are two-sided, and a p-value of less than 0.05 is considered to indicate statistical significance. Treatment differences will be displayed by hazard ratios, odds ratios, and 95% confidence intervals. All the analyses will be performed with the use of SAS® software, version 9.4 (SAS Institute).

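### The protocol contradicts itself on which children the treatment-response biomarkers cover: the synopsis sets no limit, but three body sections restrict them to children aged 4 and over with acceptable lung function

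*Protocol*

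**What the plan says.** **Without a limit.** The protocol synopsis ends its key secondary endpoints with "result of TRACK, CGI-C at end of treatment and potential biomarkers for treatment response" and then names eosinophils, total IgE and specific IgE to common allergens. It attaches no age or lung-function condition. Footnote 1 of the trial schedule defines the Visit 1 panel, including the differential blood count and "creatinine levels and total serum IgE and specific IgE to birch, grass", again with no age limit. Section 5 (Visit 1 investigations) and section 6.3.3 set none either.

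**With a limit.** Sections 3.4, 6.1 and 8.3 each carry a second list headed "Additional secondary endpoints for children aged 4 years and older". Its first sentence reads "Only applicable for patients able to perform technically acceptable (and reproducible) pulmonary function tests". Two FEV1/FVC bullets follow, and the third bullet is "Potential biomarkers for treatment response (Eosinophils, IgE, specific IgE to common allergens".

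**Method.** Section 8.3.2 names negative binomial regression for three count endpoints and Cox regression for exacerbation-free survival. For the rest it says "Further secondary endpoints will be assessed by chi-square or Fisher's exact test for categorical variables or t-test or Mann-Whitney-U-test for continuous variables". It does not mention the biomarkers by name. Section 8.3.3 leaves subgroups to the SAP as a possibility.

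**The concern.** An eosinophil count or IgE level does not require a child to perform spirometry, so the condition looks misplaced for these markers. The same bullet sits in the same place in three sections, so an analyst working from the body text would drop the 1- to 3-year-olds, while one working from the synopsis would keep them.

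The question matters to this trial. Section 1.1 argues that tiotropium works irrespective of IgE and eosinophils, and that this is of special interest in preschool asthma because raised values are less common there than in school-age asthma. Leaving out the younger part of the trial population would weaken the trial's ability to examine that argument.

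The method raises a second question. A marker for treatment response asks whether the drug effect differs by marker level. A two-sample test on the marker itself does not estimate that.

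**Working it through.** **1. The plan's own figure.** The protocol gives no number for the biomarker analysis, so I first checked its sample size. Section 8.1 gives 90% and 75% with an event at one year, hazard ratio 0.60, loss hazard 0.16, two-sided alpha 0.05 and power 0.80. I assume 1:1 allocation, which is not stated.
- Events (Schoenfeld): 4 × (1.960 + 0.842)² / (ln 0.60)² = 120.3, so 121.
- Control hazard: −ln(0.10) = 2.303. Tiotropium hazard: 0.60 × 2.303 = 1.382.
- Event probability with competing loss over one year: (2.303/2.463) × (1 − e^−2.463) = 0.855 and (1.382/1.542) × (1 − e^−1.542) = 0.704; mean 0.780.
- N = 121 / 0.780 = 155.2, rounded up to 156. A Lakatos-type log-rank calculation also gives 156, with 79.3% power at 152.

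The stated 152 therefore reproduces within 3%, and the planning rates can be used below.

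**2. Size of the restricted group.** Section 6.2 (spirometry) reports that "74.6% of the children aged 4–6 years could perform at least 2, repeatable measurements in the healthy status". The protocol does not give the share of children aged 4 or 5. An even spread over five one-year bands gives 2/5 = 40%.
- Central case: 152 × 0.40 × 0.746 = 45 children.
- Low: 152 × 0.30 × 0.60 = 27. High: 152 × 0.50 × 0.90 = 68.
- Expected events, if rates do not depend on age: 152 × 0.780 = 118.5 in all children, and 45.4 × 0.780 = 35.4 in the restricted group.

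**3. What a two-sample test of a Visit 1 marker between arms can show.** Visit 1 precedes randomization, so any difference between arms is chance. A 500-run simulation used the planning rates, a 50:50 marker and a true ratio of hazard ratios of 0.3 (strong effect modification):

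| Test | n = 152 | n = 46 |
|---|---|---|
| Marker compared between arms, rejections | 6.0% | 4.8% |
| Treatment-by-marker interaction in Cox model, rejections | 90% | 37% |

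The first row is the nominal error rate within simulation error. That test does not react to differential response.

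**4. Power of the interaction.** With a 50:50 marker and 1:1 arms, SE(log ratio of hazard ratios) = 4/√events: 4/√118.5 = 0.367 and 4/√35.4 = 0.672. Power = Φ(|ln R|/SE − 1.960).

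| True ratio R | All 152 | About 45 |
|---|---|---|
| 0.5 | 47% | 18% |
| 0.3 | 91% | 43% |
| R detectable with 80% power | 0.36 | 0.15 |

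The last row is exp(−2.802 × SE).

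**The case against.** **The restriction may be intended.** The bullet just above the biomarkers defines response as a 10% improvement in FEV1 or FVC. If the biomarkers refer to that response, only children who can do spirometry have the outcome, and the limit is coherent. This reading is possible. It fits the synopsis poorly, because the synopsis lists the biomarkers but no FEV1/FVC endpoint. Even if it is right, synopsis and body still describe different populations and need reconciling.

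**The method belongs to the SAP.** Section 8 sends analysis details there and lets the SAP modify the plan, section 8.3.1 leaves further Cox covariates to it, and section 8.3.3 leaves subgroups to it. This stands. A reader might infer that the trial cannot show which children respond. The documents do not support that, because the unseen SAP could specify interactions in all children.

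**Section 8.3.2 does not say that the arms are compared.** This also stands. The biomarkers reach the two-sample tests only through the catch-all sentence, which names no groups. Responders against non-responders would fit the same words, but pooled over arms that comparison would show prognosis and not differential response to tiotropium. Nor can one assume a planned end-of-treatment comparison of IgE: footnote 1 specifies IgE at Visit 1 only, and section 6.3.3 assigns no visit.

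**No data are lost.** Correct. Blood is drawn without an age limit, subject to the cap on puncture attempts. What is at stake is the analysis population.

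**The power figures describe an analysis the protocol does not plan.** Also correct. They show what the narrower population would cost if an interaction were examined, and they do not criticise a stated power.

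**Conclusion.** The contradiction over population holds and can be seen on the page: no limit in the synopsis and the Visit 1 panel, against a double limit in sections 3.4, 6.1 and 8.3. Taken literally, the body text leaves about 45 of 152 children, or 27 to 68 with 30–50% of children aged 4 or 5 and 60–90% spirometry success. Those ranges are assumptions. The 74.6% comes from 4- to 6-year-olds when healthy, whereas trial children are symptomatic.

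On method the conclusion is narrower. The one approach the protocol assigns, by default, is a two-sample test; used on Visit 1 markers between arms, it cannot show differential response. That is not proof that the question will go unanswered, because the SAP may add the right analysis. The event and power figures rest further on 1:1 allocation, a 50:50 marker split and event rates that do not vary with age; the documents establish none of these.

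**What to change.** 1. In sections 3.4, 6.1 and 8.3, move the biomarker bullet to the list of secondary endpoints for all patients, so that it agrees with the synopsis. If markers of FEV1/FVC response were also meant, keep that as a separate item for children able to do spirometry.
2. In section 8.3.2, state that Visit 1 eosinophils, total IgE and sensitization will be examined as exploratory treatment-by-marker interactions in the Cox model for time to first severe exacerbation, in the ITT population.

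This costs a wording change, made by amendment as section 11.5.2 requires for an ongoing trial, and a few extra models on data already collected. It adds no visit or blood draw and leaves the primary analysis as it is. The drawback is low power even in all 152 children, so the results must be labelled exploratory. Naming markers and model before unblinding limits selective reporting.

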3. It is not necessary to perform lung function if the medical files provide clear evidence that the patient is not able to perform technically acceptable lung function. Lung function measurements are performed -10 minutes prior to trial drug administration and 30 minutes post-dose at visit 2 only.
4. Spirometry / oscillometry will be performed -10 minutes prior to trial drug administration and 30 minutes, post-dose at visit 2.
5. Each Respimat® inhaler contains drug supply for 30 days.
6. In order to reduce the burden of parents, the electronic diary does not have to be filled out daily all year round. It is well known from many studies that asthma exacerbations occur particularly in autumn, winter and spring. For this reason, the diary does not have to be kept for 4 months in the months of May, June, July and August. If the patients are recruited in the summer months, they only need to keep an electronic diary between visit 1 and visit 2.
7. The CGI-C should be completed prior to other visit assessments and should precede any discussions with a health professional (physician or nurse).
8. Levels of asthma control will be measured as described in the GINA guideline.
9. The following data are collected during telephone contacts: compliance of study medication use, health status, AEs, concomitant diseases and treatments, concomitant therapies, and medication, and exacerbations.
10. The screening period (between visit 1 and visit 2) may be extended by 7 days (see flow chart), e.g. for administrative reasons.
11. All patients must be symptomatic (partly controlled or uncontrolled) as defined by the GINA guideline for children aged 5 years and younger (7) at visit 1 (screening) and before randomization at visit 2. If this criterion is not met at visit 2, the visit can be repeated once within 2 weeks.
12. In case of severe asthma exacerbation or severe respiratory tract infection (or any other acute illnesses) defined by systemic steroid intake or hospitalization in the 4–6 weeks prior to visit 2, the randomization visit (visit 2) must be postponed until 4 weeks following recovery from the infection or exacerbation.

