## **3 TRIAL DESIGN**

This is a prospective randomized, double-blind, placebo-controlled, parallel-group trial (a non-commercial trial, clinical phase III) to evaluate the safety and efficacy of Tiotropium inhalation solution (2.5 µg) administered once daily via Respimat® Inhaler for 52 weeks to prevent severe asthma exacerbations in patients 1–5 years with uncontrolled or partially controlled preschool asthma and at least one severe asthma exacerbation requiring hospitalization and/or was treated with 2 courses of systemic steroids in the last 24 months before visit 1 (three days of oral systemic steroids or one day of rectal prednisolone).

[figure not shown]

**Figure 2:** Trial design

After signing informed consent and completing an initial screening visit (Figure 2, V1), patients enter a 4–6 week screening period to ensure clinical stability (i.e. no severe exacerbations). Patients who meet all inclusion criteria and do not present with any of the exclusion criteria will be randomized into the 52-week treatment period (V2) in which they will be assigned at random to one of the two treatment groups. Additional clinic visits will be scheduled at 6, 16, 28, 40, and 52 weeks after start of therapy (V2). A telephone contact will be scheduled between V4 and V5, V5 and V6, and V6 and V7.

Pulmonary function tests (PFTs) will be performed in patients  $\geq 4$  years who are capable of providing PFTs of acceptable quality. Spirometry/Oscillometry measurements will be performed in patients  $\geq 4$  years if they are capable of providing measurements of acceptable quality (with a mouthpiece) and if the required equipment is available at site.

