## Determination of primary and secondary measures

**The primary efficacy endpoint** is the time to first severe exacerbations defined by hospitalization and/or at least 3 days of systemic steroids or one day of rectal prednisolone (Rectodelt®). Severe exacerbations were chosen as primary outcome because they are patient-important outcomes that have significant consequences for children, caregivers, and the health care system.

**Key secondary endpoint(s) for all patients:** Secondary endpoints for all patients:

- Number of severe exacerbations
- Exacerbation-free survival time defined as the time from randomization until the first severe exacerbation.
- Percentage of patients requiring systemic corticosteroid rescue for asthma during the 52-week treatment period.
- Number of hospitalizations (severe exacerbation).
- Percentage of days and episodes of > 3 days with use of PRN salbutamol rescue medication during 52-week treatment period (non-severe exacerbation).
- Percentage of days without asthma symptoms assessed by TIPP diary App (PACD).
  - A day without asthma symptoms is defined as a day during which the patient experienced no asthma symptoms (daytime and overnight; question 1, 2, 5, 6, did not use rescue medication (salbutamol) (question 3 and 7), and had no asthma exacerbation/worsening requiring systemic corticosteroids, an unscheduled visit to a doctor's office, or hospital (question 11).
- Percentage of night-time awakenings due to asthma symptoms as assessed by the TIPP diary App.
- Health utilization defined as number of physician visits during treatment.
- Number of missed days in daycare.
- Number of asthma-related events defined by use of antibiotics.
- Evaluation of TRACK at V1, at V4 and at end of treatment.
- CGI-C at end of treatment.

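### The 30-minute FEV1/FVC endpoint is worded as a within-child pre/post contrast, and Section 8.3.2 does not turn it clearly into a comparison of tiotropium with placebo

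*Protocol*

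**What the plan says.** Sections 3.4, 6.1 and 8.3 of the Protocol carry the same bullet among the additional secondary endpoints for children aged 4 years and older: FEV1 and FVC "measured 30 minutes post IMP will be compared to pre-dosing FEV1 and FVC values at visit 2". No arm is named, and no change score or responder variable is defined. In Section 8.3 the bullet belongs to the endpoint list headed "Determination of primary and secondary measures".

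The tests are in Section 8.3.2. This endpoint is not mentioned there and falls under the general rule: "Further secondary endpoints will be assessed by chi-square or Fisher's exact test for categorical variables or t-test or Mann-Whitney-U-test for continuous variables". On reporting, the section says: "Treatment differences will be displayed by hazard ratios, odds ratios, and 95% confidence intervals". It also sets the decision rule: "All tests are two-sided, and a p-value of less than 0.05 is considered to indicate statistical significance".

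The data for a controlled comparison exist. Footnote 4 of the Trial Schedule says "Spirometry / oscillometry will be performed -10 minutes prior to trial drug administration and 30 minutes, post-dose at visit 2", and Section 3 describes the design: "This is a prospective randomized, double-blind, placebo-controlled, parallel-group trial". Children in both arms who can perform the test therefore have both readings.

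**The concern.** The endpoint sentence and the trial ask different questions. The sentence, followed literally, tests whether FEV1 or FVC changes over the interval around the first dose. The trial needs to know whether that change differs between tiotropium and placebo. If anything other than the drug moves the readings in both arms, the first null hypothesis is false even when tiotropium does nothing at 30 minutes.

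Section 8.3.2 does not settle which question is tested. The Mann-Whitney U test compares two independent groups, which points to the arms. But the reader has to supply the variable to be compared, and neither of the two named effect measures suits a continuous change in litres. If the listed tests were applied to the contrast as the bullet words it, two readings from one child would be treated as independent.

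At stake is the only acute lung-function endpoint in the plan. With the wording open, a significant within-arm change could be reported as an acute bronchodilator effect although the randomised control had not been used.

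**Working it through.** **The protocol's own figures.** The protocol gives no sample size, variability or expected effect for this endpoint. Its one sample size, 152, belongs to the primary endpoint and does not bear on this point.

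**Setting the passages side by side.** Write Y0 for the pre-dose value, Y1 for the 30-minute value and D = Y1 − Y0. Four analyses could be taken from the text:

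| Reading | Null hypothesis | Fit with the endpoint sentence | Fit with Section 8.3.2 |
|---|---|---|---|
| Paired test of D, in one arm or pooled | mean D = 0 | yes | no: no paired test is named |
| Unpaired t-test or Mann-Whitney U of Y1 against Y0 | same distribution before and after | yes, literally | test named, but the two samples are the same children |
| Two-sample test of Y1 between arms | same Y1 in both arms | no: the pre-dose value is not used | yes |
| Two-sample test of D between arms | same mean D in both arms | only if the sentence is read as defining D | yes, but D is not named as the variable |

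Only the last two use the placebo arm as control. Only the last uses both the control and the pre-dose value, and no sentence in the protocol states it.

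**Why a pre/post test does not isolate the drug.** Suppose the drug has no effect and D has mean s × SD in both arms, where SD is the standard deviation of D.

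- The paired t-statistic on n children has noncentrality s × √n, so rejection rises with n for any non-zero s.
- The between-arm difference in mean D has expectation s × SD − s × SD = 0, so a two-sample test of D keeps its 5% level whatever s is.

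**Illustration.** The inputs are assumptions, not protocol figures: 20 or 30 evaluable children per arm, s from 0 to 0.8, normal data, and a two-sided 5% level (Section 8.3.2). Results are from 20,000 simulated trials per setting with no drug effect:

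| Shift s | Paired test, tiotropium arm (n = 20 / 30) | Paired test, arms pooled (n = 40 / 60) | Two-sample test of D between arms |
|---|---|---|---|
| 0 | 5% / 5% | 5% / 5% | 5% / 5% |
| 0.2 | 14% / 19% | 24% / 33% | 5% / 5% |
| 0.4 | 40% / 57% | 70% / 86% | 5% / 5% |
| 0.8 | 92% / 99% | over 99% / over 99% | 5% / 5% |

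**Hand check at s = 0.4, n = 20.** Noncentrality is 0.4 × √20 = 1.79, and the critical value of t on 19 degrees of freedom is 2.09. The noncentral t distribution then gives a rejection probability of 0.397, against 0.399 simulated. For the pooled test with n = 40, noncentrality is 0.4 × √40 = 2.53, which gives 0.694 against 0.701 simulated.

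With no shift, every test holds its level. The excess comes entirely from s, about which the protocol is silent.

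**The case against.** The strongest reply is that the bullet defines a measure and not a test. It stands in a list of measures whose other bullets, such as TRACK, CGI-C and missed daycare days, also name no arms, and nobody doubts that those are to be compared between arms. The trough bullet beside it likewise refers to the visit 2 pre-dose value to define a response. Section 8.3.2 then offers "t-test or Mann-Whitney-U-test for continuous variables", names no paired test, and speaks of treatment differences in a parallel-group trial. A two-sample test of the change fits all of this and behaves well. Section 8 leaves analysis detail to the SAP, which is not shown.

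Much of this stands. A reader might infer that the protocol has fixed an uncontrolled within-child analysis and excluded tiotropium versus placebo. The documents do not support that, because Section 8.3.2 leaves a between-arm test of change open.

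A reader might also infer that a false bronchodilator finding is likely. That is not supported either:

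- The repeatability limit in Section 6.2 (0.1 L or 10%) describes variability, not a systematic rise.
- The wash-out in Section 4.2 precedes both readings.
- The benzalkonium chloride in both inhalers (Section 4.1.4) would, if anything, lower the readings.

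The reply does not remove the mismatch. This bullet differs from its neighbours: it states what is compared with what, and its comparator is the child's own earlier value. The trough bullet uses that value to form a per-child response; this one forms no variable. Section 8.3.2 supplies neither the variable nor a usable effect measure. The SAP may repair this, but it is built on the protocol and could equally carry the sentence forward.

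**Conclusion.** The concern holds as a mismatch between the endpoint definition and the analysis section. The only contrast stated for this endpoint is post-dose against pre-dose. The between-arm comparison of change has to be inferred, and the pre-dose value has no stated place in the analysis.

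If the sentence were followed literally, a significant result would not be evidence of a tiotropium effect. The table shows how far that could go, but its size rests on assumed shifts and numbers of children, so it is not an estimate of error in this trial.

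The point is minor. It affects one secondary endpoint, in children aged 4 or over who can perform acceptable lung function at a site with the equipment. The primary analysis and the sample size are unaffected.

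**What to change.** In Sections 3.4, 6.1 and 8.3, define the endpoint as the change in FEV1 and in FVC from pre-dose to 30 minutes post-dose at visit 2, compared between tiotropium and placebo.

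In Section 8.3.2, or in the SAP before unblinding, analyse each change by a linear model (ANCOVA) with treatment and the pre-dose value as covariate. Report the adjusted mean difference with its 95% confidence interval. Show within-arm changes descriptively, without a test.

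The cost is one sentence in three places and one line in the analysis section. No new measurement is needed, because both readings are already scheduled in both arms. The one thing given up is the option of reporting a significant within-arm change as an effect. Section 8 requires a protocol amendment only for major changes to the primary endpoint or its analysis, so the SAP could carry the clarification. Correcting the endpoint sentence as well keeps the two documents consistent.
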